#### Randomization and blinding

Participants will be randomly allocated in a 1:1 ratio, stratified according to study centre and gestational age (<26 weeks or ≥26 weeks), and using random permutated blocks. Multiple birth infants will be randomized independently, unless parents or legal representatives explicitly request that siblings are to be allocated to the same treatment arm. Randomization and drug supply management is performed via an electronic online platform (ALEA®, FormsVision BV, Abcoude, the Netherlands).

Once the participant has been randomized, a study medication kit will be allocated. All treatment kits will be visually identical and contain either doxapram or placebo. The clinical trial centre and trial pharmacy of the Erasmus Medical Centre will manage the randomization list. The parents, researchers and medical team will have no access to the randomization list. Unblinding is only performed by an independent safety officer in emergency situations where knowledge of the study drug is considered absolutely necessary for the clinical management of the included patient.

#### Statistical analysis

### Primary outcome analyses

Baseline patient and clinical characteristics will be collected. Continuous variables will be presented as mean and standard deviation if normally distributed, and as medians and interquartile range if not normally distributed. The Kolmogorov-Smirnov test will be performed to assess normality of continuous variables. Categorical variables will be presented as frequencies and percentage. A difference with a *p* <0.05 is set as statistically significant.

Primarily, intention-to-treat analyses will be performed. Per-protocol and as-treated analyses will be performed secondarily if needed. The conditional odds ratio will be calculated from a multivariable logistic regression model, adjusted for the stratification factors gestational age and centre, to assess the treatment effect of doxapram on the primary outcome. The 95% confidence interval of the conditional odds ratio will be based on the profile likelihood and a *p*-value will be based on the likelihood ratio test. Hospitals with fewer than ten participants with the composite primary outcome at 18 to 24 months corrected age will be combined in this analysis, to ensure that the parameter estimates converge and increase stability. Parents of twins are able to choose whether they prefer randomization of both infants separately, or in the same treatment arm. In both cases, twins will be analysed as individuals ignoring the correlation between them [36].

The average absolute risk reduction will be estimated from the logistic regression model using the method of standardization to calculate the risk of an adverse outcome in both study arms by taking the difference. The 95% confidence interval for this estimate will be calculated using a bootstrap with 5000 replicates and will be based on the quantiles of the effect estimates across the bootstrap samples. The number needed to treat will be derived from the average risk difference by inverting the number. The point estimate and confidence interval for the relative risk reduction will also be calculated in a similar way as for the average absolute risk reduction, but now taking the quotient instead of difference between the estimates in both arms.

Additionally, the effect of doxapram on the primary outcome will be adjusted for important risk factors for neurodevelopmental impairment, based on the literature and our clinical experience. A multivariate logistic regression model will be computed including the independent variables small for gestational age, sex, and intraventricular haemorrhage in addition to the stratification variables [5, 37, 38]. A complete case analysis will be conducted if less than 10% of the randomized patients has missing data. In case of a higher rate of missing data, multiple imputation with sensitivity analyses will be conducted.

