#### Sample size calculation

The sample size calculation is based on a cohort study that investigated the long-term neurodevelopmental outcome of preterm infants who received doxapram therapy compared to non-treated matched control patients [20]. This paper described that 30% of the doxapram-treated patients had the composite outcome death or neurodevelopmental delay at 2 years corrected age compared to 50.8% in the non-treated control patients. We therefore consider an absolute decrease of 15% in the composite outcome as clinically relevant, and we aim to reduce the outcome from 50 to 35% with a number needed to treat of around 7 patients. With an alpha of 0.05 and a power over 80%, a sample size of 170 patients is needed per treatment arm when we use a continuity correction. Because we expect approximately 10 patients to be part of twins and a loss to follow-up rate (excluding death) of 10% per treatment arm, the sample size is 198 patients per treatment arm, adding up to a total of 396 patients to be included. Next to the formal consent letter, an animation and flyer are designed providing additional study information to optimize consent and to reach the targeted sample size.

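### Twins placed in the same arm at parental request are analysed as independent infants, which makes the primary inference slightly anti-conservative

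*Protocol article*

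**What the plan says.** All places are in the protocol article.

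- **Randomization and blinding.** Independent randomisation is the default for multiples, "unless parents or legal representatives explicitly request that siblings are to be allocated to the same treatment arm".
- **Primary outcome analyses, allocation of twins.** The parental option is repeated: "Parents of twins are able to choose whether they prefer randomization of both infants separately, or in the same treatment arm". The next sentence fixes the analysis: "In both cases, twins will be analysed as individuals ignoring the correlation between them". A reference is cited in support.
- **Primary outcome analyses, inference.** The odds ratio comes from a logistic model adjusted for gestational age and centre, with a profile-likelihood interval and a likelihood ratio p-value. The interval for the absolute risk reduction is to be "calculated using a bootstrap with 5000 replicates", using quantiles. The resampling unit is not named.
- **Sample size calculation.** The plan expects "approximately 10 patients to be part of twins and a loss to follow-up rate (excluding death) of 10% per treatment arm", and moves from 170 to 198 per arm.

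The article describes no family-clustered analysis of the primary outcome, not even as a sensitivity analysis.

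**The concern.** A single rule covers two situations that behave differently. When siblings are randomised independently, some pairs land in the same arm and some are split. Positive correlation raises the variance of the treatment contrast in the first kind and lowers it in the second, so on average ignoring it does little. When parents ask for the same arm, one allocation fixes the treatment of both infants and no split pairs offset it. A likelihood that counts the two infants as independent then understates the variance.

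What is at stake is the p-value and interval for the primary outcome, judged at 0.05. A result close to that threshold would be open to the objection that the standard error was too small. The number of same-arm pairs is decided by parents, so the design does not limit it.

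**Working it through.** **1. The plan's own figures.** Inputs from the sample size section: 50% versus 35%, alpha 0.05 (taken as two-sided), power 80%. The usual two-proportion formula without continuity correction gives 170 per arm. (With the correction that the section mentions it gives 183, which is a separate matter.) Then (170 + 10) × 1.10 = 198. This reproduces the final size and supports reading the 10 as twin infants per arm.

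**2. Formula.** Take n infants per arm, a share s of them in enrolled pairs, a share q of pairs in the same arm, and within-pair correlation ICC. There are s·n pairs in total. Each same-arm pair adds 2·ICC·σ² to the variance of the difference in arm totals, and each split pair subtracts the same amount. So

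Var = 2nσ² + s·n·2·ICC·σ²·[q − (1 − q)] = 2nσ² × DE, with DE = 1 + s × ICC × (2q − 1).

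The planned test uses DE = 1. Its true two-sided type I error is 2 × [1 − Φ(1.96/√DE)].

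**3. Inputs.** s = 10/198 = 5.1%, from the plan. ICC and q are not given and are assumptions. If a share r of pairs is requested same-arm and the rest split evenly, q = r + (1 − r)/2.

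**4. Results at the planned twin count.**

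| Pairs requested same-arm | q | ICC | DE | Type I error |
|---|---|---|---|---|
| none | 0.50 | any | 1.000 | 5.0% |
| half | 0.75 | 0.5 | 1.013 | 5.1% |
| all | 1.00 | 0.2 | 1.010 | 5.1% |
| all | 1.00 | 0.5 | 1.025 | 5.3% |
| all | 1.00 | 1.0 | 1.051 | 5.6% |

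In the last row the standard error should be √1.0505 = 1.025 times the one used, that is 2.5% larger.

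**5. Simulation check.** An unadjusted likelihood ratio test was simulated with 356 analysed infants, 10 twin infants per arm and 100,000 runs per scenario.

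- All pairs same-arm: 5.25% at ICC 0.3 and 5.5% at ICC 0.6.
- Pairs randomised independently: 5.0% to 5.1%.
- No twins: 4.8%.

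**6. Power.** At ICC 1 with all pairs same-arm, 170 × 1.0505 = 178.6, so 179 per arm. The plan provides 170 + 10 = 180 before loss to follow-up. The allowance covers the power loss but leaves the variance used by the test unchanged.

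**7. If twins are commoner than planned (assumed shares, every pair same-arm).**

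- Twice the planned share (20/198), ICC 0.5: DE = 1.051, type I error 5.6%.
- Share 30%, ICC 0.5: DE = 1.15, type I error 6.8%.

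The article gives no reason to expect either share.

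**The case against.** The strongest reply is that the simplification is disclosed, prespecified, supported by a citation and harmless at the planned twin count. Most of that stands. The plan expects few twins, independent randomisation is the default, and all pairs same-arm is an upper bound. Two further points weaken the concern:

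- The model adjusts for gestational age and centre, which twins will usually share, so the relevant ICC is the residual one.
- With permuted blocks within strata, siblings randomised consecutively are split more often than not. With an assumed block size of 4, the concordant share is 3/4 × 1/3 + 1/4 × 1/2 = 37.5%. With ICC 0.5 and no requests, DE = 1 − 0.0505 × 0.5 × 0.25 = 0.994 and type I error is 4.9%. Default pairs therefore partly offset requested ones.

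The cited source is not available here, so whether it covers same-arm pairs cannot be judged. The reply does not remove the point that the rule is applied equally to the case where no cancellation occurs.

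A reader might also infer three stronger things that the article does not support:

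- **That the sample size section contradicts the analysis.** It says only that "we expect approximately 10 patients to be part of twins". It never says that the 10 are added because twins are not independent, and enlarging a sample for twins while analysing infants individually is not a contradiction.
- **That the bootstrap certainly breaks up families.** Infant-level resampling is the natural reading of an analysis of individuals, but the unit is not stated and its absence is not a fault in an article.
- **That the inflation is material as planned.** That needs twin shares and request rates from outside the document.

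**Conclusion.** The point holds, at a modest size. The stated rule is unsound for pairs placed in one arm at parental request and nearly harmless for pairs randomised independently. At about 10 twin infants per arm, type I error lies between about 5.0% and 5.3% for an assumed ICC up to 0.5, with a ceiling of about 5.6%. To call the planned p-value and intervals simply wrong would go too far. They are slightly anti-conservative to the extent that same-arm pairs dominate, and slightly conservative if split pairs do. The size rests on the planned twin count read as per arm, and on assumed values for the ICC and for the share of requests. Since the article limits neither twins nor requests, the primary inference should not depend on both staying low.

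**What to change.** Replace the rule that ignores the correlation:

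- Keep the logistic model with the same covariates. Take the p-value and 95% interval from GEE or cluster-robust standard errors with the mother as cluster and singletons as clusters of one. With an independence working correlation the odds ratio estimate is unchanged; only its standard error differs. Higher-order multiples are handled the same way.
- Resample mothers, not infants, in the 5000 bootstrap replicates.
- Report the independence analysis (likelihood ratio test, profile likelihood) as a sensitivity analysis.

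If the sponsor prefers to keep the planned test as primary, the minimum is to prespecify the family-clustered analysis as a sensitivity analysis before unblinding, so that the choice cannot appear driven by the result.

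The cost is a family identifier in the dataset and some wording in the analysis plan. Trial conduct and sample size do not change. The downside is that a robust Wald or score test replaces the likelihood ratio test, and the interval becomes slightly wider if same-arm pairs dominate: at most 2.5% in standard error at the planned twin count. In return, the inference is valid for any mix of same-arm and split pairs.

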#### Primary outcome

The primary outcome is the composite outcome of death or severe disability at 18 to 24 months corrected age.

Severe disability will be defined as having one or more of the following outcomes at the age of 18 to 24 months: cognitive delay, cerebral palsy, severe hearing loss, or bilateral blindness. Cognitive delay will be defined as a Mental Development Index score of less than 85 on the Bayley Scales of Infant and Toddler Development III [27]. Cerebral palsy will be diagnosed if the patient had a non-progressive motor impairment, characterized by abnormal muscle tone and decreased range or control of movements. The level of gross motor function will be determined with the Gross Motor Function Classification System and is defined as severe movement disability if the score is > level 2 [28].

Severe hearing loss will be defined as hearing loss requiring hearing aids and will be measured by audiometry in patients with signs of hearing abnormalities at the corrected age of 18 to 24 months [29]. Hearing will be assumed to be normal in participants with a normal hearing screening after birth and no signs of hearing abnormalities at the corrected age of 18 to 24 months. Severe visual impairment or blindness will be defined as a corrected visual acuity less than 20/200 [30].

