### Secondary long-term outcomes

Additional long-term outcomes at 18 to 24 months corrected age will be hospital readmissions, weight, length and head circumference and behavioural problems according to the Child Behavior Checklist [33]. The cognitive and language development will be assessed by the parent-reported PARCA-R questionnaire [34].

Moreover, we will carry out an analysis of cost-effectiveness, including an analysis of health-related quality of life (HRQoL). The potential health and economic gains of doxapram could be substantial due to the low price of doxapram (off-patent) and because it is expected to result in both shorter duration of ventilation, a decrease in length of hospital stay, improved life-long neurological development and less long-term medical needs. We will explore the plausibility of this hypothesis by performing a cost-utility analysis alongside the trial.

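### A 10% cut-off decides whether missing primary outcomes are imputed and tested for sensitivity, and the trial's own planned loss falls just below it

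*Protocol article*

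**What the plan says.** All references are to the protocol article.

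- Primary outcome analyses, lower branch: "A complete case analysis will be conducted if less than 10% of the randomized patients has missing data".
- Same section, upper branch: "In case of a higher rate of missing data, multiple imputation with sensitivity analyses will be conducted". Below the cut-off no check on the missing outcomes is named.
- Primary outcome: "The primary outcome is the composite outcome of death or severe disability at 18 to 24 months corrected age". Death by itself is an event.
- Sample size calculation: the trial allows for "a loss to follow-up rate (excluding death) of 10% per treatment arm", so deaths are not counted as loss.
- The primary analysis is by intention to treat. It reports a conditional odds ratio from logistic regression, with a standardized absolute risk reduction, a number needed to treat and a relative risk reduction.

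**The concern.** The cut-off looks only at how many infants are missing, not at who they are or why. In this composite an infant known to have died is never missing, so missingness depends on one component of the outcome. Removing missing infants gives deaths more weight in each arm. The size of that shift depends on the arm's mortality and on its loss among survivors.

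Two things follow. The absolute risks, and the number needed to treat built on them, can drift even when survivors are lost at random. If loss differs by arm, or by disability in ways that differ between arms, the treatment effect is distorted too.

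The cut-off also sits almost exactly where the trial expects its loss to fall. The count of missing infants, known only at the end, would choose the primary method. On the lower side an analysis labelled intention-to-treat drops randomized survivors with no stated check.

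**Working it through.** **1. Planned loss against the cut-off.** The sample size section gives 170 per arm, about 10 for twins (read as per arm) and 10% loss. (170 + 10) × 1.10 = 198, which reproduces the stated figure. The loss allowance is 198 − 180 = 18 per arm, so 36/396 = 9.1%: complete case applies. If 10% means 10% of survivors, with assumed mortality of 5–20%, the share of randomized infants is 0.10 × 0.95 = 9.5% down to 0.10 × 0.80 = 8.0%, again below. If it means 10% of all randomized, the expected count is 39.6 and the lower branch covers 39 or fewer. Binomial P(39 or fewer of 396) is 0.50 at a true rate of 10% and 0.73 at 9.1%. Read literally, exactly 10% falls in neither branch.

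**2. Complete-case risk.** Per arm, with proportions of those randomized:

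risk = [D + S(1 − a)] / [D + S(1 − a) + U(1 − b)]

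D is deaths, S disabled survivors, U unimpaired survivors; a and b are the loss rates in S and U. The event rates are the protocol's ("we aim to reduce the outcome from 50 to 35" percent: true difference 15.0 points, true odds ratio 0.538). Mortality and the pattern of loss are not in the document and are assumed throughout.

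**3. Equal random loss, 9.1% of randomized.** With 15% mortality in both arms, a = b = 0.0909/0.85 = 0.107.
- Placebo: (0.15 + 0.35 × 0.893)/0.909 = 50.9%.
- Doxapram: (0.15 + 0.20 × 0.893)/0.909 = 36.1%.
- Difference 14.7 points, odds ratio 0.546.

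Equal mortality of 10% and 20% gives 14.8 and 14.6 points. Mortality of 20% v 5% gives 15.9 points and odds ratio 0.520. If deaths are the same share of events in both arms and survivor loss rates are equal, the odds ratio stays at 0.538.

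**4. Loss unequal between arms, no true effect, 3% v 15%.** Event rates 42.5–50%, mortality 10–25%.
- Low end (mortality 10%, risk 50%, loss as a share of survivors): 0.488/0.973 = 50.2% v 0.440/0.865 = 50.9%, a spurious 0.7 points.
- Mortality 25%, risk 45%, loss as a share of randomized (4% v 20% of survivors): 0.442/0.970 = 45.6% v 0.410/0.850 = 48.2%, or 2.7 points.
- The high end, at risk 42.5%, is 2.8 points.

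Total missing is 6.7–9.0%, so complete case would apply in every one of these cases.

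**5. Disability-linked loss in opposite directions, no true effect.** In one arm 5% of disabled and 16% of unimpaired survivors are lost; in the other arm the reverse. With mortality 10% and risk 50%: 0.480/0.900 = 53.3% v 0.436/0.911 = 47.9%, or 5.5 points. With mortality 25% and risk 42.5%: 46.3% v 42.1%, or 4.2 points. Average missing is 0.105 × (1 − mortality), so 7.9–9.45%, again below the cut-off.

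**6. Can the planned loss reverse a result?** Take 90/180 v 63/180 observed, 18 missing per arm, uncorrected chi-square (p=0.004).

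| Events among 18 lost placebo / 18 lost doxapram | Completed table | Difference | p |
|---|---|---|---|
| 0 / 7 | 90/198 v 70/198 | 10.1 | 0.041 |
| 0 / 8 | 90/198 v 71/198 | 9.6 | 0.052 |
| 7 / 14 | 97/198 v 77/198 | 10.1 | 0.043 |
| 7 / 15 | 97/198 v 78/198 | 9.6 | 0.055 |
| 0 / 18 | 90/198 v 81/198 | 4.5 | 0.36 |
| 18 / 0 | 108/198 v 63/198 | 22.7 | <0.001 |

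The planned test is an adjusted likelihood ratio test, so these p-values are indicative.

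**The case against.** The strongest reply is that the harm is small under ordinary loss. The primary measure is an odds ratio, which step 3 shows is unbiased or nearly so when survivors are lost alike in both arms and regardless of disability. The trial is double blind with a blinded outcome assessor and plans the same loss in each arm, so 3% v 15%, or disability-linked loss in opposite directions, is a hard case. The reversals are demanding too. With an assumed 30 deaths per arm, observed disability in survivors would be (63 − 30)/150 = 22% on doxapram and (90 − 30)/150 = 40% on placebo. Losing significance needs 8/18 (44%) v 0/18, or 15/18 (83%) v 7/18 (39%), among those lost. All of that stands, and it limits the size of the point.

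A reader might infer four stronger things that the document does not support:

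- **Complete case is necessarily biased because only survivors can be lost.** It can be biased. Material distortion of the effect needs loss that differs by arm or by disability, and its direction cannot be known in advance. A late death may also go unrecorded after withdrawal.
- **Sensitivity analyses are ruled out below 10%.** They are only not named there, and an analysis plan not shown may add them.
- **The method turns on one or two infants.** That holds only if 10% of all randomized infants are lost. At the 36 in the protocol's arithmetic, four more would be needed to leave the lower branch. Missing data are also not defined as outcome data alone, so missing covariates could count.
- **Imputation alone would cure the problem.** Under a missing-at-random assumption it does not remove disability-linked bias, which produces the largest shifts above.

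What the reply does not answer is why a percentage should decide whether benign loss is checked at all. This is a rule the protocol states, not a detail left to the analysis plan.

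**Conclusion.** The point holds as a cheap improvement to a stated rule, not as a demonstrated bias. The cut-off is poorly placed: by the protocol's own arithmetic the planned loss (9.1%) lands on the side with no named check. Under equal random loss the effect estimate barely moves, and absolute risks are overstated by roughly one point. Arm-dependent loss shifts the difference by about 0.7–2.8 points and opposed disability-linked loss by about 4–5.5, against a 15-point target. These ranges rest on assumed mortality of 10–25% and assumed loss patterns. Loss of the planned size can overturn a result at the planned effect, but only with markedly unequal outcomes among the missing infants.

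**What to change.** Remove the 10% switch and state one approach for any amount of missing primary outcome data:

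- Keep known deaths as events. Multiply impute disability in survivors without an assessment, separately by arm, from variables already collected: gestational age, centre, sex, small for gestational age, intraventricular haemorrhage and BPD.
- Add parent-reported scores where available. The protocol plans them: "The cognitive and language development will be assessed by the parent-reported PARCA-R questionnaire", and behaviour scores as well. They are measured at the same age as the primary outcome, so many lost infants may lack them.
- Add a delta-adjusted tipping-point analysis, because imputation under missing at random does not address disability-linked loss.
- Report complete case as a sensitivity analysis.

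The cost is a change of wording before unblinding and a little extra analysis. No new data and no change in sample size are needed.
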